## Abstract

**Background::**

Stroke is one of leading diseases causing adult death and disability worldwide. Home-based telerehabilitation has become a novel approach for stroke patients as effective as conventional rehabilitation, and more convenient and economical than conventional rehabilitation. However, there is no study assessing the mechanism of home-based telerehabilitation in promoting motor recovery among stroke patients with hemiplegic.

**Aims::**

This study is designed to determine the efficacy and explore the mechanism of motor recovery after home-based telerehabilitation in stroke patients with motor deficits.

**Methods/Design::**

In a single-blinded randomized controlled pilot study, patients with acute subcortical stroke (n = 40) are assigned to receive home-based telerehabilitation or conventional rehabilitation. Task-based or resting-state functional magnetic resonance imaging (rs-fMRI), diffusion tensor imaging (DTI), and Fugl–Meyer assessment (FMA) score will acquired before and after rehabilitation. Activation volume of bilateral primary motor (M1), supplementary motor area (SMA), premotor cortex (PMC); lateralization index (LI) of interhemispheric M1, SMA, and PMC; functional connectivity of bilateral M1, SMA, PMC; fractional anisotropy (FA) will be measured; correlation analyses will be performed between neuroimaging biomarkers and FMA score pre- and postrehabilitation.

**Discussion::**

We present a study design and rationale to explore the effectiveness and neural mechanism of home-based rehabilitation for stroke patients with motor deficits. The study limitations related to the small-amount sample. Moreover, home-based rehabilitation may provide an alternative means of recovery for stroke patients. Ultimately, results of this trial will help to understand the neural mechanism of home-based telerehabilitation among stroke patients with hand movement disorder.

## Background

1

Stroke is characterized by its high morbidity, disability, and mortality rate, which brings serious damage on human health.^[1,2]^ Statistics data revealed that the disability rate of stroke can reach up to 60% to 80%, enormously decreasing quality of life for survivals.^[3,4]^ Numerous studies showed that patients who undertook early rehabilitation treatment can to some extent have a lower disability rate and better improvement of daily living activities.^[5–7]^ However, majority of stroke patients have no access to effective rehabilitation due to the limits of traditional rehabilitation sources under the current state of health care construction in China. Furthermore, the therapeutic effects of rehabilitation treatment in stroke patients are poor because of relative high costs of traditional rehabilitation and the difficulty in adhering to rehabilitation treatment on account of the fatigue of commuting rehabilitation training institution and family.^[8]^ Telerehabilitation could facilitate the access to rehabilitation treatment, no matter where and when, improving patients’ compliance and chances of recovery.^[9,10]^

Task-based functional magnetic resonance imaging provides an effective approach to studying brain active region.^[11]^ Longitudinal task-based fMRI measurements could provide qualitative, quantitative, and dynamic information about conditions of remaining neurons during the process of recovery, including monitoring activation state of each related cerebral cortex qualitatively and dynamically, as well as measuring activation volume of motor area quantitatively and dynamically.^[12]^ Resting-state functional magnetic resonance imaging (rs-fMRI) is widely applied to investigate integration network of brain function.^[13]^ It could dynamically reflect the changes of brain motor function network connection.^[14]^ Diffusion tensor imaging (DTI) is a noninvasive method used to study microstructure, providing dynamic information about the recovery state of lesioned brain tissue qualitatively and quantitatively.^[15]^

Our previous research and other numbers of studies have shown that acute stroke patients undertaking home-based rehabilitation could achieve equal effects compared with traditional rehabilitation, in terms of effectiveness of neurologic function improvement, degree of stress relief of caregivers and safety of rehabilitation implementation.^[16–18]^ To further explore the mechanisms of home-based telerehabilitation in improving neurological functions of stroke patients, our study investigated dynamic changes of motor activated region, changes of motor functional connectivity, and structural changes of white matter fiber in patients with motor deficits by means of task-based fMRI, rs-fMRI, and DTI.

We designed this study to provide more robost evidence of the application of home-based rehabilitation on patients of stroke with motor deficits.

### Methods/design

1.1

#### Study design

1.1.1

The trial is an assessor blinded, paralleled randomized controlled trial (RCT). The overall flowchart is shown in Figure 1. The main aim is to explore the mechanisms of home-based telerehabilitation on improving neurological functions of stroke patients. The secondary objective is to determine the effects of home-based telerehabilitation in stroke patients.

**Figure 1 F1:**
[figure not shown]
The flow scheme of study.

### Ethics approval and consent to participate

1.2

This trial follows the principal ethical guidelines for conducting clinical trials of Helsinki Declaration and has received approval from the Independence Ethics Committee of the Fifth Peoples’ Hospital of Shanghai, Fudan University (ethic approval number: 2014-ETRE-066) and has been registered in the Chinese Clinical Trial Registry (ChiCTR-IPR-17011757). Any issues related to clinical study safety will be reported to the Ethics Committee in time, such as the changes of clinical protocols or patient information. Participants will be acquainted with informed consent and asked to sign for it before being recruited.

### Randomization and blinding

1.3

#### Randomization

1.3.1

In this pilot study, we aim to collect 40 patients diagnosed as stroke from the Department of Neurology, Shanghai the Fifth People's Hospital, Fudan University. Patients included in the study will be randomly allocated into 2 groups in a ratio of 1:1 after baseline assessment: home-based rehabilitation group and conventional rehabilitation group. An independent statistician will conduct randomized allocation by using a computer. The former will receive exercise training rehabilitation and electromyography-triggered neuromuscular stimulation with the assistance of caregivers at home. Specialist physicians will evaluate the recovery condition of patients via telerehabilitation system every week and give guidance on rehabilitation training and electro-stimulation therapy. The latter will receive the same rehabilitation training under the guide of specialist physicians face to face. Specialist physicians will evaluate the recovery condition of patients at outpatient clinic every week and adjust the rehabilitation strategies. Allocation concealment will be guaranteed, since allocation information will be protected in opaque sealed envelopes by a specially assigned person who is not involved in the study.

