#### Inclusion criteria

1.4.1

1.First-ever stroke and in stable condition after acute management of ischemic stroke.2.Aged between 35 and 85, male or female.3.Responsible focuses of the unilateral white matter area indicated by cranial CT or MRI.4.No more than 14 days from stroke onset, with unilateral limb movement dysfunction and be proved to be right handed after standardized testing.5.National Institute of Health Stroke Scale (NIHSS) scores from 2 to 20, Grading Muscle Strength of paralyzed upper limbs between grade 1 and grade 4, and have not received any standard rehabilitation intervention before inclusion.6.Sign the informed consent by the patient himself or voluntarily.

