#### Primary outcome

1.6.1

Primary outcomes will be conducted before and after rehabilitation therapies, including sum of bilateral activated volume of primary motor (M1), supplementary motor area (SMA), premotor cortex (PMC) (V_M1+SMA+PMC_); lateralization index (LI) of interhemispheric M1, SMA, and PMC (LI_M1+SMA+PMC_)(LI = (ΣV_C_ − ΣV_I_)/(ΣV_C_+ ΣV_I_), subscripts C and I refer to contralateral and ipsilateral hemisphere responses, respectively. The ΣV measures the regional activation level associated with the activated voxel); functional connectivity of bilateral M1, SMA, PMC, and the value of fractional anisotropy (FA) in corticospinal tract (CST) at ipsilesional posterior limb of internal capsule. Data will be collected before (at basement) and after (3 months) rehabilitation.

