### Data analyses

1.9

Data analysis will be handled by independent statisticians who are blind to the groups. The statistical tests will be 2-side and at the 5% significance level. Means and standard deviation will be used for statistical description of continuous variables. For fMRI data, independent sample *t*-test or independent sample rank test will be used for grouped comparison of quantitative data. Pearson correlation coefficients (*r*) will be used to determine whether patients’ functional connectivity correlated with their FMA score and be computed after application of Fisher's *r*-to-*z* transform to yield variates that are approximately normally distributed (*z* = 0.5 ln[(1+*r*)/(1−*r*)]). All the statistical analysis will be carried out by the SPSS software (Armonk, NY). For DTI data, statistical analyses will be performed using nonparametric permutation testing (Randomize in FSL) with 5000 Monte Carlo simulations. We looked for differences in FA between the groups accounting for age, time of stroke onset, and NIHSS as regressors of no interest in the general linear model.

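### FA is adjusted for stroke severity, but the three fMRI primary outcomes are compared unadjusted in a 40-patient trial whose article describes no balancing on severity

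*Protocol article*

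**What the plan says.** Section 1.3.1 sets the size ("we aim to collect 40 patients diagnosed as stroke"), the ratio and timing ("Patients included in the study will be randomly allocated into 2 groups in a ratio of 1:1 after baseline assessment") and the method ("An independent statistician will conduct randomized allocation by using a computer"), with concealment in sealed envelopes. It mentions no stratification, blocking or minimisation. It does not call the randomisation simple or unrestricted either.

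Section 1.4.1 admits "National Institute of Health Stroke Scale (NIHSS) scores from 2 to 20", so the score is an eligibility item and is available before allocation.

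Section 1.6.1 lists four kinds of primary outcome: activated volume, lateralization index and functional connectivity from fMRI, and FA from diffusion imaging. All are measured before treatment and at 3 months.

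Section 1.9 treats the two modalities differently. FA is compared "accounting for age, time of stroke onset, and NIHSS as regressors of no interest in the general linear model". For fMRI data, an independent-samples t-test "or independent sample rank test will be used for grouped comparison of quantitative data". On error control it says "The statistical tests will be 2-side and at the 5% significance level".

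**The concern.** Severity is controlled for one kind of primary outcome and left uncontrolled for the other three, and the article gives no reason for the difference. NIHSS is collected on every patient, so the information is there and goes unused.

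In two arms of 20 drawn from a wide severity range, noticeable differences in mean NIHSS will often arise by chance. If NIHSS is related to an fMRI outcome, two things follow. The part of the outcome's variation that severity explains stays in the error term, so the comparison is less precise than it could be. And if the one allocation actually drawn is unbalanced, the stated test has no means of correcting for it, which makes the result hard to interpret. In a trial this small, the lost precision matters.

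**Working it through.** **Inputs from the article:** 40 patients at 1:1, so n = 20 per arm; NIHSS 2 to 20; two-sided 5% tests; no covariate for fMRI. The article gives no power calculation, effect size or SD, so there is no stated figure to reproduce.

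**Assumptions not in the article:** correlation r between NIHSS and the fMRI quantity compared (0.1 to 0.7), and the shape of the NIHSS distribution (uniform on 2–20 with SD 5.5, or right-skewed with mean 6.4 and SD 3.1).

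**1. Chance imbalance without balancing.** The standardised difference in mean NIHSS has SE = √(2/20) = 0.316.
- P(difference > 0.3 SD) = 2[1 − Φ(0.3/0.316)] = 34%.
- P(difference > 0.5 SD) = 2[1 − Φ(0.5/0.316)] = 11%.
- 95% range: ±1.96 × 0.316 = ±0.62 SD.

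In NIHSS points (simulated), a difference of 2 or more occurs in 25% of allocations with uniform scores and 4% with skewed scores.

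**2. What an imbalance does to the unadjusted comparison.** An imbalance of 0.5 SD shifts the contrast by 0.5 × r outcome SD: 0.15, 0.25 and 0.35 for r = 0.3, 0.5 and 0.7. The simulated false-positive rates of the t-test were:

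| r | imbalance > 0.5 SD | imbalance < 0.1 SD | all allocations |
|---|---|---|---|
| 0.3 | 7–8% | about 4% | 5% |
| 0.5 | 13–14% | about 2.4% | 5% |
| 0.7 | 21–23% | about 1% | 5% |

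The test is too liberal after a bad draw and too conservative after a good one. Over all draws it holds its level.

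**3. Gain from NIHSS as a continuous covariate.** Relative to the unadjusted comparison, the variance of the arm difference is multiplied by (1 − r²) × [1 + 1/(38 − 2)]. Here 38 is the within-arm degrees of freedom, and the second factor (1.028) is the price of estimating the slope, for a roughly normal covariate.

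| r | variance ratio | change in variance | unadjusted total with the same precision |
|---|---|---|---|
| 0.1 | 0.99 × 1.028 = 1.018 | +1.8% | 40/1.018 ≈ 39 |
| 0.3 | 0.91 × 1.028 = 0.935 | −6.5% | 40/0.935 ≈ 43 |
| 0.5 | 0.75 × 1.028 = 0.771 | −23% | 40/0.771 ≈ 52 |
| 0.7 | 0.51 × 1.028 = 0.524 | −48% | 40/0.524 ≈ 76 |

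Simulation gave 6–7%, 23% and 46–49% at r = 0.3, 0.5 and 0.7. For an assumed standardised effect of 0.8, power rises from 72% unadjusted to about 76%, 83% and 94% (normal approximation, without the 1.028 factor, so slightly optimistic).

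**4. Gain from stratifying allocation at the median instead.** Stratification cuts the simulated SE of the NIHSS difference from 1.730 to 0.897 points (uniform) or from 0.975 to 0.658 (skewed). The variance ratios are (0.897/1.730)² = 0.269 and (0.658/0.975)² = 0.455. The outcome variance falls by r² × (1 − ratio):
- Uniform: r² × 0.731 = 7%, 18% and 36% at r = 0.3, 0.5 and 0.7.
- Skewed: r² × 0.545 = 5%, 14% and 27%.

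At r = 0.5 and above, the continuous covariate does better than the median split, and it leaves allocation untouched.

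**The case against.** **The article is condensed.** Its silence on strata does not show that none exist; the full protocol may block or stratify. A reader might infer from section 1.3.1 that severity is ignored at allocation, but the text supports only that no balancing is described. This objection stands, and it is why the point rests on section 1.9, where the unadjusted fMRI test is stated outright.

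**The nuisance-covariate statement belongs to the FA model only.** A reader might take it as an admission that severity drives all the imaging outcomes. The article does not say so, and it gives no correlation between NIHSS and any fMRI measure. What stands is the unexplained difference in treatment between the modalities.

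**Randomisation already protects the test.** This is correct on average. A reader might think a severity imbalance would push results towards a treatment effect. Chance imbalance is symmetric and hides an effect as readily as it mimics one.

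**Baseline imaging could absorb severity.** If pre-post change is compared, part of a baseline difference cancels. The article does not say whether change or 3-month values enter the fMRI test. The r used above should then be read as the correlation of NIHSS with whatever is compared, which could be low, and at 0.1 adjustment gains nothing.

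**An unadjusted comparison is acceptable in a 40-patient pilot.** It is valid. But the plan already adjusts FA for severity, so consistency asks little.

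**Conclusion.** The point holds as one of precision and consistency in section 1.9. Three of the four kinds of primary outcome are compared without the severity control given to the fourth, and the described allocation does not supply it either. If allocation is in fact unbalanced, mean NIHSS will differ by more than 0.5 SD in about 11% of allocations; that figure depends only on 20 per arm and a normal approximation.

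The gain from adjustment depends on an assumed correlation: small at 0.3, material at 0.5 and 0.7, and a loss of 1–2% near 0.1. The documents do not support a claim of systematic bias or of an inflated overall type I error, nor a firm statement that the trial does not stratify.

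**What to change.** In section 1.9, replace the t-test or rank test for activated volume, lateralization index and functional connectivity with a linear model containing treatment arm and baseline NIHSS as a continuous covariate, matching the severity control already used for FA. This needs no new data and no change to allocation. It costs one degree of freedom and about 1–2% of precision if NIHSS turns out to be nearly unrelated to the outcome.

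Optionally, if the full protocol does not already do so, state in section 1.3.1 that allocation uses permuted blocks within two NIHSS strata with a cut-point fixed in advance. That means two allocation lists and two envelope series, slightly more administration, and a possible small departure from 20:20 where blocks are left incomplete. If the full protocol already stratifies, one sentence in section 1.3.1 should say so.

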#### Blinding

1.3.2

In this study, a specific device during home-based telerehabilitation will be adopted; the patients and home-based rehabilitation therapists cannot be blinded. To ensure the research quality, the assessors and data analysts are totally blind to allocation and rehabilitation intervention until they finish all the data collection and analyses.

### Participants

1.4

#### Inclusion criteria

1.4.1

1.First-ever stroke and in stable condition after acute management of ischemic stroke.2.Aged between 35 and 85, male or female.3.Responsible focuses of the unilateral white matter area indicated by cranial CT or MRI.4.No more than 14 days from stroke onset, with unilateral limb movement dysfunction and be proved to be right handed after standardized testing.5.National Institute of Health Stroke Scale (NIHSS) scores from 2 to 20, Grading Muscle Strength of paralyzed upper limbs between grade 1 and grade 4, and have not received any standard rehabilitation intervention before inclusion.6.Sign the informed consent by the patient himself or voluntarily.

#### Exclusion criteria

1.4.2

1.Glasgow Coma Scale (GSC) scores less than 15, have dementia indicated by Minimum Mental State Examination (MMSE) assessment, have mental disorders and be unable to cooperate with examination or treatment.2.Motorial and sensory disturbance not induced by stroke or induced by previous ischemic stroke.3.Serious comorbidity like malignant tumor, primary cardiac, hepatic, renal or hematopoietic system diseases.4.History of cognitive disorder, psychiatric disorders, drug abuse and alcoholism.5.Infections or ruptures on the skin of forearms or legs.6.Have a heart pacemaker, metal stent, plate or an implant that is susceptible to the current pulse in the body.7.Be pregnant or lactant or have birth plans recently.8.Be long-term musical conductors or keyboard operators before stroke onset.9.Have claustrophobia.10.Be unable to finish basic course, or be hard to maintain compliance and follow-up.

### Intervention

1.5

Intervention measures were described in detail in our previous studies.^[19]^ Rehabilitation therapies include exercise rehabilitation training and electromyography-triggered neuromuscular stimulation (ETNS).

#### Exercise rehabilitation training

1.5.1

All patients will receive Brunnstrom motor function grading evaluation by the same rehabilitation therapist after discharged from hospital. Individualized rehabilitation training plans will be made based on specific conditions of each patient, including physical therapy (PT) and occupational therapy (OT). Patients will be given corresponding treatment based on the Brunnstrom stages. Patients receive the designated exercise rehabilitation for 45 minutes, once a day for 5 days a week for 3 months.

#### ETNS

1.5.2

ETNS is a novel method developed from the combination of myoelectric biofeedback technology and neuromuscular electrical stimulation (NMES), which has outstanding features compared to NMES. It can increase stroke patients’ initiatives in taking rehabilitation training and effectively improve motor function of the affected limb and ability of daily living, so it has becomes a new therapeutic option in treating paralyzed patients. Patients in both groups will receive ETNS 20 minutes each time, twice a day for 5 days a week for 3 months. The MyoNet-AOW biofeedback equipment used in our study has been approved by China Food and Drug Administration (Shanghai food drug supervision character 2010 no. 221114).

### Outcomes

1.6

#### Primary outcome

1.6.1

Primary outcomes will be conducted before and after rehabilitation therapies, including sum of bilateral activated volume of primary motor (M1), supplementary motor area (SMA), premotor cortex (PMC) (V_M1+SMA+PMC_); lateralization index (LI) of interhemispheric M1, SMA, and PMC (LI_M1+SMA+PMC_)(LI = (ΣV_C_ − ΣV_I_)/(ΣV_C_+ ΣV_I_), subscripts C and I refer to contralateral and ipsilateral hemisphere responses, respectively. The ΣV measures the regional activation level associated with the activated voxel); functional connectivity of bilateral M1, SMA, PMC, and the value of fractional anisotropy (FA) in corticospinal tract (CST) at ipsilesional posterior limb of internal capsule. Data will be collected before (at basement) and after (3 months) rehabilitation.

#### Secondary outcome

1.6.2

Fugl–Meyer assessment (FMA) score will be assessed as secondary outcome. The FMA score consists of 17 items, ranging from 0 to 34, with lower scores demonstrating poorer movement function.

### Data acquisition and preprocessing

1.7

Data will be acquired by a Siemens 3.0T Magnetom Trio scanner (Siemens Medical Solutions). Subjects will receive 2 MRI sessions (1 before and 1 after rehabilitation therapy). Each session included 1 rs-fMRI scan, 1 task functional scan and 1 DTI scan. For fMRI scan, parameters are TR/TE/FA = 1500 ms/30 ms/90°, 200 time points, resolution = 3.4 × 3.4 × 5 mm^3^, 21 axial slices. During rs-fMRI scan, patients will be asked to keep away with the eyes closed and think of nothing. The motor task scans used a block design paradigm consisting of alternating 30-seconds periods of performance of an isometric precision grip task and rest for 4 minutes. DTI images will be acquired with the following parameters: matrix size = 94 mm × 94 mm, field of view = 240 mm × 240 mm, 2.6 mm slice thickness, 56 slices. We acquired 1 set of 30 diffusion weighted images with a *b*-value = 1000 s/mm^2^, and 5 no diffusion weighted images.

All data will be analyzed using Functional MRI of the Brain (FMRIB's) Software Library (FSL) tools. Functional data sets will undergo slice timing correction, motion correction, scaling to percent signal change, smoothed with a Gaussian kernel of 8 mm full-width-at-half maximum, bandpass temporal filtering (0.01–0.08 Hz), and grand mean intensity normalized. A whole brain analysis of white matter integrity between groups will be performed to investigating FA. FA quantifies the degree to which water diffusion will be restricted and calculated based on the diffusion tensor. The data will be corrected for head motion and eddy current distortion, and brain extracted using Brian Extraction Tool. FA images will be then created by fitting the data to a tensor model at each voxel using DTI fit within the FMRIB's Diffusion Toolbox. Lesion will be masked out in each subject's data so that all analyses are performed on nonlesioned data.

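### The 0.01–0.08 Hz band-pass is written for all functional data, including the task run, where it inflates activated volume and pulls LI towards zero unless the degrees of freedom are corrected

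*Protocol article*

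**What the plan says.** All of the relevant text is in the protocol article, section 1.7 (Data acquisition and preprocessing).

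- Runs per session: "Each session included 1 rs-fMRI scan, 1 task functional scan and 1 DTI scan".
- Acquisition: one parameter set, "For fMRI scan, parameters are TR/TE/FA = 1500 ms/30 ms/90°, 200 time points". It is not split between the resting and the task run.
- Task: a "block design paradigm consisting of alternating 30-seconds periods of performance of an isometric precision grip task and rest for 4 minutes".
- Preprocessing: "Functional data sets will undergo slice timing correction, motion correction, scaling to percent signal change", followed by smoothing and "bandpass temporal filtering (0.01–0.08 Hz), and grand mean intensity normalized". The chain is given for functional data in general. No other chain is given for the task run.

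Section 1.6.1 makes two task-run measures primary outcomes: the bilateral activated volume of M1, SMA and PMC, and LI, the contralateral minus ipsilateral activation divided by their sum. Section 1.9 compares quantitative fMRI measures between groups by a t-test or rank test at the two-sided 5% level.

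**The concern.** A 0.01–0.08 Hz band-pass suits connectivity analysis of resting data. On a block-design run it acts unevenly: the task signal sits inside the retained band, while most of the noise spectrum is discarded. A first-level model that still counts every volume as a degree of freedom then understates residual variance and overstates each voxel's t statistic.

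Activated volume depends on which voxels are declared active, and LI is built from the same activation. Surplus voxels on both sides enlarge the volume. In LI they add equally to both terms of the difference and to the denominator, so LI shrinks towards zero. The main aim is mechanism, with 40 patients, so what these two measures actually capture matters.

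A smaller question concerns run length: the stated volumes and TR do not give the stated task duration, and the text does not say which run the 200 volumes describe.

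**Working it through.** **Inputs from section 1.7.** TR 1.5 s; "200 time points"; 30 s task and 30 s rest alternating for 4 minutes; band 0.01–0.08 Hz.

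**Assumptions.** The article gives no voxel threshold or noise model, so these are assumed: one-sided thresholds t > 2.3 and t > 3.1, or nominal p < 0.001; white or AR(1) noise with correlation 0, 0.3 or 0.5; a haemodynamically convolved block regressor, filtered like the data.

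**1. Run length.** 200 × 1.5 s = 300 s = 5 min. The paradigm is 4 min = 240 s, and 240 / 1.5 = 160 volumes. The difference is 40 volumes (60 s).

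**2. What the filter keeps.**
- Nyquist frequency: 1 / (2 × 1.5) = 0.333 Hz. Retained share: (0.08 − 0.01) / 0.333 = 21%.
- Bins: 17 of 81 at 160 volumes, 22 of 101 at 200.
- The task cycle is 60 s, or 0.0167 Hz. This frequency and its third harmonic (0.05 Hz) lie inside the band; the fifth (0.083 Hz) lies just outside.
- Design variance retained: 98.2% at 160 volumes, 98.8% at 200.

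**3. Expected inflation at 160 volumes, white noise.** Each retained bin carries two dimensions, so residual df = 2 × 17 − 1 = 33, against a nominal 160 − 2 = 158. The t statistic is inflated by √(158 / 33) = 2.19. A cut-off of 2.3 therefore acts like 2.3 / 2.19 = 1.05 on 33 df, which has an upper-tail probability of 15.0%, against a nominal 1.1%. A cut-off of 3.1 acts like 3.1 / 2.19 = 1.42, giving 8.3% against a nominal 0.1%.

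**4. Simulation of null voxels, 160 volumes, white noise (share above threshold).**

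| Filter and model | t > 2.3 | t > 3.1 |
|---|---|---|
| Band-pass, ordinary linear model | 15.0% | 8.2% |
| Band-pass, AR(1) prewhitening | 7.0% | 2.4% |
| High-pass only, ordinary linear model | 1.3% | 0.1% |
| High-pass only, AR(1) prewhitening | 1.6% | 0.2% |

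A separate run at t > 2.3 gave 14.6%, 6.9%, 1.3% and 1.6%. The first row agrees with step 3.

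**5. Other noise settings, nominal p < 0.001 (160 or 200 volumes, correlation 0 to 0.5).**
- Band-pass, ordinary model, nominal df: 7–10%.
- Band-pass, AR(1) prewhitening: 2–4%.
- Band-pass, Tukey-taper prewhitening: 9–11%.
- Band-pass, df set to the retained frequencies (33 or 43): 0.1–0.3%.
- High-pass, AR(1) prewhitening: 0.2–0.4%.
- High-pass, ordinary model, correlation 0.5: 3.4–3.8%, so high-pass filtering also needs prewhitening when noise is coloured.

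**6. Effect on volume and LI.** Illustrative signals with contralateral above ipsilateral activation; 160 volumes, correlation 0.3, p < 0.001. High-pass with AR(1) prewhitening is compared with band-pass and uncorrected df in an ordinary model.

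| Scenario | Active share C / I, high-pass | Active share C / I, band-pass | LI, high-pass | LI, band-pass |
|---|---|---|---|---|
| 1 | 0.358 / 0.070 | 0.700 / 0.410 | 0.67 | 0.26 |
| 2 | 0.500 / 0.028 | 0.755 / 0.282 | 0.90 | 0.46 |
| 3 | 0.234 / 0.008 | 0.609 / 0.159 | 0.93 | 0.59 |

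Scenario 1, for example: (0.700 − 0.410) / (0.700 + 0.410) = 0.26. Volume rises and LI falls in all three.

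**The case against.** **The first-level model is not shown.** A journal article may leave the model, threshold and df rule to a fuller document. That is fair, and their absence is not the point here. With df set to the retained frequencies the null rate returns to about nominal, so the harm is conditional. But the filter itself is a stated choice, written for all functional data, and prewhitening alone did not remove the inflation.

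**The task signal survives.** It does: 98% or more of the design variance is kept. The problem is not lost signal but noise removed without the matching loss of df.

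**LI may not be a pure voxel count.** Section 1.6.1 describes its terms as an activation level tied to activated voxels. The direction of the effect carries over, because the set of active voxels still depends on the threshold; the exact size need not.

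Three stronger readings are tempting and are not supported:

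- *LI is inflated.* It is attenuated, as the illustrations show.
- *Treatment effects will be masked, or false ones created.* The filter is identical in both arms and analysts are blinded (sections 1.3.2 and 1.9), so between-arm type I error is not inflated. Loss of sensitivity depends on the model. In a small simulation (160 volumes, correlation 0.3, t > 3.1, three signal levels), standardised group differences with high-pass against band-pass, both AR(1) prewhitened, were 0.65 vs 0.63, 0.94 vs 0.88 and 0.87 vs 0.80 for volume, and 0.51 vs 0.49, 0.48 vs 0.48 and 0.48 vs 0.48 for LI. Larger losses came mainly with the band-pass and an uncorrected ordinary model (volume 0.50, 0.59, 0.32; LI 0.49, 0.31, 0.24), and the article does not say that this model is used.
- *The acquisition is wrong by a minute.* The 200 volumes may describe only the resting run, since the next sentence turns to that run, or the task run may carry a further minute of rest. The text states neither.

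**Conclusion.** The point holds, with a condition. As written, section 1.7 applies the band-pass to the task run. If the first-level model keeps nominal degrees of freedom, null voxels pass an assumed t > 2.3 at about 15% (ordinary model) or 7% (AR(1) prewhitened) rather than about 1.3–1.6%, under white noise and 160 volumes. The inflation appeared at every threshold and noise setting tried.

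The result is an overstated activated volume and an LI drawn towards zero. This harms the validity of two primary outcomes and possibly their sensitivity. The sizes rest on assumed noise, thresholds and signals; the direction does not depend on the particular values tried. It deserves correction before analysis but does not threaten the type I error of the group comparison.

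The 5-minute against 4-minute difference is secondary: a description to be reconciled, not a demonstrated acquisition error.

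**What to change.** In section 1.7:

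- Limit the 0.01–0.08 Hz band-pass to the rs-fMRI data.
- For the task run, specify high-pass filtering only, with a cut-off below the task frequency of 1/60 Hz (for example 0.01 Hz), together with prewhitening. Alternatively, keep the band-pass and state that the first-level model sets its degrees of freedom to the retained frequencies.
- State the number of volumes and the duration separately for the resting and the task run. If the task run does have 200 volumes, say what the last 60 s contain.

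The cost is a few lines of text and, if processing has begun, re-processing the task data from raw. No new scans are needed.
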